### Sample size calculation

The sample size was calculated using PASS software (version 11, Kayesville, UT, USA) [27]. As the primary efficacy outcome, the EMA recommend using both TAC and the number of HDD [1]. Besides, any reduction in total alcohol consumption of at least 10 g/day for patients with alcohol use disorders will reduce the annual and lifetime risk of alcohol-related death [28].

In this context, the sample size calculation based on an expected difference between the treatment groups of 15 g/day in total alcohol consumption or 3 days per month, with a standard deviation for the TAC of 30 g/day and with an autocorrelation of 0.3 to 0.7 between observations in the same subject, between 82 and 122 patients, would be required.

Considering a significance level of 1.25% (co-primary outcome) and a power of 80%, and with the hypothesis of a premature withdrawal or a non-initiation of treatment (acute repeated alcoholism) for 20% of individuals, 144 patients (72 per group) should be included to meet the objectives of the study.

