### Statistical analysis

All randomized participants will be analyzed regardless of the treatment allocated (intention to treat analyses (ITT)) and after excluding patients with deviation from the protocol (per-protocol analyses (PP)).

The main analysis will be carried out with the intention to treat population. The co-primary outcome of change from baseline in TAC and reduction in the number of HDD at 4 weeks after treatment and its association with rTMS will be analyzed under the intention-to-treat principle using a mixed model for repeated measures.

The baseline and demographic characteristics of the two groups (active rTMS vs sham rTMS) will be described in terms of numbers and percentages and quantitative variables in means and standard deviations, or medians and interquartile intervals. The comparability of the two groups at baseline will be evaluated using the chi-squared test or Fisher’s test for qualitative variables, and Student’s T test or the Wilcoxon-Mann-Whitney test for continuous variables. Then, a mixed model repeated measures will be conducted to estimate the effect of treatment on TAC first, and HDD second. Observed cases will be considered random effects, and site, sex, time, and treatment as fixed effects. We will use multiple imputation techniques to compensate for potential bias introduced by missing endpoint data [29].

For the primary outcome, per-protocol analysis will also be conducted among participants who have completed baseline and endpoint assessments. The secondary outcome measurements will be analyzed with similar models to those used for the co-primary, continuous variables and logistic regression for dichotomized outcomes.

No interim analysis is planned.

All tests will be one-sided. The primary results will be examined at a significance level of 0.0125 (co-primary outcome). For secondary outcomes, the threshold for significance will be fixed at 0.025. All analyses will be performed using SAS version 9.4 (SAS Institute Inc) by the team of statisticians of the Unité de Soutien Méthodologique, Direction of Clinical Research, University Hospital of Dijon, France. Statistical code will not be made public.

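### After the stated 20% loss, 144 patients leave about 115, seven short of the 122 that the protocol itself requires at an autocorrelation of 0.7

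*Protocol article*

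**What the plan says.** The section Sample size calculation of the protocol article gives its inputs in two steps.

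- First, the requirement. It assumes an "expected difference between the treatment groups of 15 g/day in total alcohol consumption or 3 days per month". The SD of TAC is taken as 30 g/day, and the autocorrelation within a subject as 0.3 to 0.7. On that basis, "between 82 and 122 patients, would be required".
- Second, the number to enrol. It takes a 1.25% significance level and 80% power, expects "premature withdrawal or a non-initiation of treatment (acute repeated alcoholism) for 20% of individuals", and concludes that "144 patients (72 per group) should be included to meet the objectives of the study".

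The Statistical analysis section adds "All tests will be one-sided" and repeats the 0.0125 level for the primary results.

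The section does not say which autocorrelation between 0.3 and 0.7 the 144 is based on, or how many repeated measures were assumed.

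**The concern.** The step from the required number to the enrolled number does not follow from the figures printed beside it. A reader who removes the stated 20% from 144 arrives below the top of the stated requirement. No autocorrelation below 0.7 is named as the planning value, so nothing in the paragraph explains why the smaller number would be enough.

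This paragraph is the only justification given for the size of the trial, and a null result would be read against its 80% power statement. If the autocorrelation is near 0.7 and loss reaches 20%, that statement is not met.

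**Working it through.** **Inputs** (protocol article, Sample size calculation and Statistical analysis): requirement 82 to 122 in total; enrolment 144 (72 per group); loss 20%; one-sided significance level 0.0125; power 80%; difference 15 g/day; SD 30 g/day; autocorrelation ρ from 0.3 to 0.7. The number of repeated measures m is not stated.

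**1. Does the range 82 to 122 already include the loss?**

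Normal approximation for two means, with m measures averaged and equal correlation between them (compound symmetry):

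N = 4 × [SD × (z₁ + z₂) / difference]² × [1 + (m − 1)ρ] / m

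Here z₁ = 2.2414 (one-sided 0.0125) and z₂ = 0.8416 (80% power), sum 3.0830. The first part is 4 × (30 × 3.0830 / 15)² = 152.08.

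Several values of m and several correlation structures were tried. Assuming m = 3:

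- ρ = 0.3: 152.08 × 1.6/3 = 81.1, so 41 per arm, **82** in total.
- ρ = 0.7: 152.08 × 2.4/3 = 121.7, so 61 per arm, **122** in total.

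Both ends reproduce exactly, with the stated level and power and with no allowance for loss. The range therefore appears to be the number needed before loss, which agrees with the order of the paragraph. The choice m = 3 is inferred, not documented.

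**2. From the requirement to enrolment**

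| Start | Divide by 0.80 | Multiply by 1.20 |
|---|---|---|
| 82 | 102.5, so 103 | 98.4, so 99 |
| 122 | 152.5, so 153 (154 with equal arms) | 146.4, so 147 |

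Division is the correct method; multiplication is a common error. Neither gives 144 from either end of the range.

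**3. From enrolment back to the requirement**

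- 144 × 0.80 = 115.2, so about 115 evaluable patients.
- 122 − 115 = 7 short.
- Largest loss at which 144 still leaves 122: 1 − 122/144 = 15.3%.

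Steps 2 and 3 use only the protocol's own figures and need no model.

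**4. Power at ρ = 0.7 with 20% loss**

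If 122 patients give 80% power, 115.2 patients give

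Φ(3.0830 × √(115.2/122) − 2.2414) = Φ(0.754) = **77.5%**.

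This needs only the ratio 115.2/122, the significance level and the normal approximation, not the value of m. Reading 1.25% as two-sided changes it little (77.3%).

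**5. Elsewhere in the range, only if the model with m = 3 is right**

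With 115.2 evaluable patients, power is about 92% at ρ = 0.3 and 85% at ρ = 0.5. It falls to 80% where 152.08 × (1 + 2ρ)/3 = 115.2, that is at ρ = 0.636.

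**The case against.** **The text does not expressly promise 80% power over the whole range.** A reader might infer that it does. In fact one sentence gives a span of requirements for a span of correlations, and the next gives 144. Choosing a point inside a sensitivity range is ordinary practice, and a condensed article may leave the choice to the full protocol. This stands as a limit on the point: the documents do not show that a worst-case guarantee was made and broken. It does not remove the mismatch, because the paragraph prints all its other figures and ties 144 to no value in the range.

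**The trial is not shown to be underpowered in general.** Under the inferred model, power is above 80% over most of the range. The shortfall needs both a high autocorrelation and the full 20% loss.

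**A larger shortfall is not supported.** A t-test calculation gives about 76% with 57 per arm, which suggests a gap of 4 points. By the same t test, however, 122 patients give only about 79%, so the like-for-like loss is about 2.5 to 3 points.

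**The limit of about 0.63 is model-dependent.** It rests on three averaged measures with compound symmetry, and the article states neither. Nor is it evident how three measures relate to a primary outcome defined over one 28-day period (Outcomes section). The limit should not be treated as the protocol's own.

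**The cause of the mismatch is unknown.** The number 144 equals 120 × 1.2 and is close to 122/0.85, but nothing in the document shows that either was used.

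**115 is not the primary analysis set.** The main analysis is by intention to treat, with a mixed model and multiple imputation. Missed visits may be made by telephone, and patients who never start treatment may still give outcome data. The power figures are therefore approximate. This does not rescue 144: the protocol's own calculation treats the 20% as lost, imputation does not restore the missing information, and untreated patients dilute the effect.

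**Conclusion.** The point holds in a limited form. On the protocol's own figures, 144 patients with 20% loss leave about 115, which is 7 below the stated upper requirement of 122. Full coverage of the range would need 153 (154 with equal arms), 9 to 10 more than planned. Otherwise loss would have to stay at or below 15.3%.

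At an autocorrelation of 0.7, power is about 77.5% instead of 80%, a loss of 2.5 points. That figure assumes that 122 is the pre-loss requirement for 80% power, and it uses the normal approximation. The first assumption is supported by the exact reproduction of 82 and 122 without any loss.

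The effect is modest and sits at one end of the range. The paragraph should still be corrected, because its figures do not connect and the correction costs almost nothing.

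**What to change.** Keep 144 and replace the concluding statement with wording such as:

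> With 144 patients randomized and 20% lost, about 115 remain evaluable. This does not reach the 122 required at an autocorrelation of 0.7, where power is about 77%. The whole range from 0.3 to 0.7 is covered at 80% power only if loss is at most about 15%.

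The sponsor should add the autocorrelation and the number of repeated measures on which 144 rests. The statement that 80% power holds up to an autocorrelation of about 0.63 should be added only if the sponsor confirms the model of three averaged measures with compound symmetry.

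The cost is the wording of one paragraph and a slightly less favourable power statement at one end of the range. No extra patients and no change to the analysis are needed.

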### Statistical analysis

All randomized participants will be analyzed regardless of the treatment allocated (intention to treat analyses (ITT)) and after excluding patients with deviation from the protocol (per-protocol analyses (PP)).

The main analysis will be carried out with the intention to treat population. The co-primary outcome of change from baseline in TAC and reduction in the number of HDD at 4 weeks after treatment and its association with rTMS will be analyzed under the intention-to-treat principle using a mixed model for repeated measures.

The baseline and demographic characteristics of the two groups (active rTMS vs sham rTMS) will be described in terms of numbers and percentages and quantitative variables in means and standard deviations, or medians and interquartile intervals. The comparability of the two groups at baseline will be evaluated using the chi-squared test or Fisher’s test for qualitative variables, and Student’s T test or the Wilcoxon-Mann-Whitney test for continuous variables. Then, a mixed model repeated measures will be conducted to estimate the effect of treatment on TAC first, and HDD second. Observed cases will be considered random effects, and site, sex, time, and treatment as fixed effects. We will use multiple imputation techniques to compensate for potential bias introduced by missing endpoint data [29].

For the primary outcome, per-protocol analysis will also be conducted among participants who have completed baseline and endpoint assessments. The secondary outcome measurements will be analyzed with similar models to those used for the co-primary, continuous variables and logistic regression for dichotomized outcomes.

No interim analysis is planned.

All tests will be one-sided. The primary results will be examined at a significance level of 0.0125 (co-primary outcome). For secondary outcomes, the threshold for significance will be fixed at 0.025. All analyses will be performed using SAS version 9.4 (SAS Institute Inc) by the team of statisticians of the Unité de Soutien Méthodologique, Direction of Clinical Research, University Hospital of Dijon, France. Statistical code will not be made public.

Data management (data entry, coding, security and storage) and statistical evaluation will be carried out by the Clinical Research Department of the Dijon University Hospital, which is a service which is independent of the care units where the patients will be treated. As this is a very low risk trial for patients, French legislation does not require the creation and monitoring of a data monitoring committee. In consequence, no auditing of trial conduct was planned.

Only the patient’s anonymous code is reported in the case report form (CRF). This is comprised of the patient’s initials (first letter of the family name and the first name), the number of the center, and the number corresponding to the position in the list of inclusions.

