### Exclusion criteria

Patients will be excluded if they have, at the inclusion visit, any of the following: (1) breath-alcohol concentration (BAC) > 0 mg per liter of exhaled air; (2) less than 6 heavy drinking days (HDD) in the previous 4 weeks (defined as more than 60 g of pure alcohol in men and 40 g in women consumed in 1 day) [1]; (3) average alcohol consumption below the medium risk level according to World health Organization (WHO) in the previous 4 weeks (≤ 40 g/day for men; ≤ 20 g/day for women) [22]; (4) more than 3 days of abstinence prior to inclusion; (5) a revised Clinical Institute Withdrawal Assessment (CIWA) for Alcohol score ≥ 10 (indicating the need for medication-supported detoxification); (6) concomitant treatment with disulfiram, acamprosate, topiramate, baclofene, naltrexone, or nalmefene; (7) a history of pre-delirium tremens and delirium tremens; (8) DSM-5 substance use disorder other than alcohol or tobacco use disorder; (9) acute psychiatric disorders that have required hospitalization and/or immediate adjustment of psychotropic medications; (10) severe major depression, as defined by 17-item Hamilton Depression scale (HAM-D) ≥ 24 [23]; (11) recent change in psychotropic medication (< 1 month); (12) severe chronic psychiatric disorders including schizophrenia, paranoia, and bipolar disorder types I and II; (13) advanced liver, kidney, cardiac, or pulmonary disease or other acute serious or unstable medical conditions that would compromise a patient’s participation in the study according to the physician’s judgment; (14) contra-indications to rTMS: personal history of convulsive seizures, cerebral vascular accident, pacemaker, neurosurgical clips, carotid or aortic clips, heart valves, hearing aid, ventricular bypass valve, sutures with wires or staples, foreign objects in the eye, shrapnel, other prosthesis, or intracranial ferromagnetic material; (15) women who are pregnant or lactating; (16) women of childbearing potential with a positive urine β–human chorionic gonadotrophin pregnancy test at inclusion; (17) concurrent participation in another trial, employees of the investigator or trial site, and patients protected by law; (18) persons who are not covered by national health insurance; (19) patients, in the opinion of the investigation, not able to complete the TimeLine Follow-Back (TLFB) and to record their daily alcohol consumption in a diary (derived from the TLFB) during the 3 months of the study; and (20) patients who refused to sign the consent form and “safety agreement”.

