### Randomization

Randomization will be performed the day of inclusion, online, using the secure CleanWeb^TM^ system by the investigator after identification though a personal password after a final check of the eligibility criteria (website https://chu-dijon.tentelemed.com). Patients will be randomly assigned to one of the two groups in a 1:1 ratio to one of two arms: rTMS active or rTMS placebo. The allocation algorithm, which relies on a minimization approach, is established by the study statistician (Unité de Soutien Méthodologique à la Recherche, USMR, Hospital University of Dijon) before the start of the trial. This allocation is stratified on center and sex. Investigators and patients will be blinded to the treatment assignment. A comprehensive document describing the randomization procedure will be kept in a confidential manner at the USMR.

Emergency unblinding will be performed in an emergency situation when the status of the brain stimulation (real or placebo) must be known to the investigator in order to provide appropriate medical treatment.

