### Outcomes

In the “*Guideline on the development of medicinal products for the treatment of alcohol dependence*” for alcohol reduction strategies, the European Medicines Agency (EMA) recommend using a co-primary efficacy outcome, change from baseline in total alcohol consumption (TAC) per month, and reduction in number of HDD [1]. Thus, our principal effective criteria on alcohol reduction will be both the change in TAC from baseline to week 4, defined as mean daily alcohol consumption over 28 days (in g/day), and the number of HDD. Baseline will be defined as alcohol consumption during the 28 days before randomization using the *alcohol Timeline Followback* (TLFB) method, a validated method that retrospectively obtains estimates of daily drinking using a calendar [25, 26]. During follow-up, patients will be asked to report their alcohol consumption on a daily basis.

The secondary evaluation criteria will be the change from baseline to the end of the rTMS sessions, and then for each 4-week period after the treatment up to week 24 in:
TAC (g/day) and number of HDDProportion of subjects with a significant categorical shift in World Health Organization (WHO) risk levels of drinking: low risk (H≤40 g/d; F≤20 g/d), medium risk (H≤60 g/d; F≤40 g/d), high risk (H≤100 g/d; F≤60 g/d, and very high risk (H> 100 g/d; F> 60 g/d) [22]Proportion of subjects with a 50%, 70%, and 90% reduction in alcohol consumption as well as the proportion of patients who potentially achieve abstinenceLevel of alcohol dependence severity (alcohol dependence scale)Craving/urge to drink assessment (visual analogue scale, obsessive compulsive drinking scale)Clinical global impression-severity and improvementScores for depression scales (HAM-D—17 items)Quality of Life (short form health survey—12 items)

Other secondary evaluation criteria will include the change from baseline at week 4, week 12, and week 24 after the treatment, in:
Biochemical alcohol consumption markers (gamma glutamyl transferase, mean corpuscular volume, aspartate aminotransferase, alanine aminotransferase, and carbohydrate deficient transferrin)Cognitive assessment (Montreal cognitive assessment)Number of cigarettes smoked/day and craving for tobacco (visual analogue scale, tobacco craving questionnaire) for smokers.

Number of patients with adverse events will be determined at the time of each visit.

No genetic or molecular analysis is planned.

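### The primary model for change in TAC and HDD omits the baseline value of the outcome, which gives up precision that the trial could have at almost no cost

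*Protocol article*

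**What the plan says.** The Statistical analysis section names both the response and the model. The response is "The co-primary outcome of change from baseline in TAC and reduction in the number of HDD at 4 weeks after treatment", analysed by a mixed model for repeated measures. The terms are then listed: observed cases as random effects, and "site, sex, time, and treatment as fixed effects". Neither baseline TAC nor baseline HDD appears. The same section plans tests of baseline comparability but attaches no adjustment to their result.

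The Outcomes section shows that the covariate exists: "Baseline will be defined as alcohol consumption during the 28 days before randomization", obtained by Timeline Followback (TLFB) calendar recall. For the period after treatment it says: "During follow-up, patients will be asked to report their alcohol consumption on a daily basis". Under Exclusion criteria, patients must be able to "record their daily alcohol consumption in a diary (derived from the TLFB"), so the follow-up record is related to the baseline instrument.

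The Randomization section says: "This allocation is stratified on center and sex". Baseline consumption is not a balancing factor.

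**The concern.** A change score uses baseline in one fixed way: it subtracts all of it, which is a slope of 1. With equal variances the best linear slope is the correlation rho between baseline and follow-up. The article's own figure for within-patient correlation is 0.3 to 0.7, well short of 1. A forced slope of 1 then has two effects.

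- The residual variance is larger than it need be, so power is lower at the same sample size.
- If the arms differ by chance at baseline, the contrast is shifted by part of that difference in the opposite direction.

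Baseline is recalled over a calendar and follow-up is recorded daily. This makes a slope of exactly 1 harder to justify.

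At stake is the chance that the trial detects the 15 g/day difference it was sized for, and how far the estimate depends on the luck of the baseline draw. The model terms are listed by name, so this is a stated choice and not a detail left open.

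**Working it through.** **Inputs** (Sample size calculation and Statistical analysis sections): difference 15 g/day in TAC; SD 30 g/day; correlation 0.3 to 0.7; one-sided alpha 0.0125 (z = 2.241); power 80% (z = 0.842); 144 patients, 72 per group; 20% loss, so 144 × 0.8 = 115.2 evaluable.

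**1. The plan's own figure.** The article states 82 to 122 patients. Per-arm n = 2(2.241 + 0.842)² × V / 15², where V = 30² × (1 + (m − 1)rho)/m is the variance of the mean of m equally correlated measures. The article does not give m; m = 3 is inferred because it returns the stated pair.
- rho 0.3: V = 480, n = 40.6, rounded up to 41, total 82.
- rho 0.7: V = 720, n = 60.8, rounded up to 61, total 122.

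This confirms alpha, sidedness, SD and difference. It concerns an average of repeated measures and contains no baseline adjustment.

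**2. Week-4 contrast if 30 g/day is the cross-sectional SD.** Assume equal variances at baseline and week 4, and that the stated correlation applies between them.
- Change score: variance 2(1 − rho) × 30².
- Baseline as covariate: variance (1 − rho²) × 30².
- Ratio of adjusted to unadjusted: (1 + rho)/2.
- Power = Φ(15 / (SD × √(4/115.2)) − 2.241).

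At rho 0.3 unadjusted: SD = 30√1.4 = 35.5, standard error 6.61, 15/6.61 = 2.27, power Φ(0.03) = 51%. Adjusted: SD = 30√0.91 = 28.6, standard error 5.33, 15/5.33 = 2.81, power Φ(0.57) = 72%.

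| rho | SD, change score | SD, adjusted | Variance ratio | Evaluable N for 80%, change score / adjusted | Power at 115.2, change score / adjusted |
|---|---|---|---|---|---|
| 0.3 | 35.5 | 28.6 | 0.65 | 214 / 140 | 51% / 72% |
| 0.5 | 30.0 | 26.0 | 0.75 | 154 / 116 | 67% / 80% |
| 0.7 | 23.2 | 21.4 | 0.85 | 92 / 78 | 89% / 94% |

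**3. Same contrast if 30 g/day is the SD of change.** The unadjusted SD is 30 at every rho; the adjusted SD is 30√((1 + rho)/2).

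| rho | SD, adjusted | Evaluable N for 80%, change score / adjusted | Power at 115.2, change score / adjusted |
|---|---|---|---|
| 0.3 | 24.2 | 154 / 100 | 67% / 86% |
| 0.5 | 26.0 | 154 / 116 | 67% / 80% |
| 0.7 | 27.7 | 154 / 130 | 67% / 75% |

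**4. Unequal variances.** With baseline SD s0 and follow-up SD s1, the unadjusted variance minus the adjusted variance is s0² + s1² − 2·rho·s0·s1 − s1²(1 − rho²) = (s0 − rho·s1)². This is never negative, so the direction does not depend on equal variances.

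**5. Chance imbalance.** With 72 per arm and cross-sectional SD 30, the standard error of the baseline difference is 30√(2/72) = 5.0 g/day. Given a baseline difference D, the change-score contrast is off by −(1 − rho)D. For D = 5 g/day the size is 3.5, 2.5 and 1.5 g/day at rho 0.3, 0.5 and 0.7, against a target of 15 g/day.

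**6. HDD.** The article gives a difference (3 days per month) but no SD, so no HDD power can be computed.

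**The case against.** **A mixed model may already use baseline.** If baseline TAC were kept in the response vector with a common mean across arms, the model would recover essentially the precision of covariate adjustment. Time is among the listed factors, so this cannot be excluded outright. But the stated response is change, which is zero at baseline by definition, and no treatment-by-time term is listed. With raw baseline in the response and main effects only, the pre-treatment difference would be averaged into the treatment effect. The text as written is the unadjusted change score.

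**The size depends on an unstated reading of the SD.** This stands. The article does not say whether 30 g/day is the SD of TAC or of its change. The unadjusted 51% and 89% belong to the first reading only, and adjusted power rises with rho under one reading and falls under the other. Both sets must be shown.

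**A single week-4 contrast is not the plan's own sample size calculation.** Also true: the 82 to 122 fit an average over repeated measures. For an average of three follow-ups under the same equal correlation, the ratio of adjusted to unadjusted variance is 0.475, 0.625 and 0.775 at rho 0.3, 0.5 and 0.7. The relative gain would then be larger than in the single contrast.

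**Stronger readings that do not hold.**
- A reader might infer that baseline imbalance is left uncorrected. It is over-corrected, and the residual is conditional on the imbalance that happens to occur.
- A reader might infer bias from regression to the mean, since eligibility depends on recent drinking. The criteria apply to both arms before randomization, so this cancels in expectation, and the article gives no figure for it.
- A reader might infer bias from a change of instrument. The diary is derived from the TLFB, and the move from recall to daily record is the same in both arms.

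**Conclusion.** The point holds as a matter of efficiency and conditional precision. Randomization keeps the planned contrast unbiased on average and type I error is not inflated, so the analysis is valid but avoidably weak. The change should be made, but the trial's validity does not depend on it.

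For TAC at week 4, adjustment cuts the variance by 35%, 25% and 15% at rho 0.3, 0.5 and 0.7. That is worth about 5 to 21 points of power if 30 g/day is the cross-sectional SD, and about 8 to 19 points if it is the SD of change. Without adjustment, this contrast falls short of the promised 80% at rho 0.3 and 0.5 under the first reading, and at every rho under the second. Adjustment reaches 80% at rho 0.5 on both readings. It does not do so at rho 0.3 on the first reading or at rho 0.7 on the second.

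These sizes assume 115.2 evaluable patients, equal variances, and that the stated correlation applies between baseline and week 4. The direction needs none of these. For HDD the same argument applies, but its size is unknown.

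**What to change.** Before unblinding, amend the model statement in the Statistical analysis section:

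- Add the matching baseline value as a fixed covariate: 28-day mean TAC in the TAC model, 28-day HDD count in the HDD model.
- If several follow-up periods are modelled together, add the interaction of baseline with period.
- Name the baseline-adjusted week-4 difference as the primary estimate for each co-primary outcome.
- Do the same for continuous secondary outcomes that have a baseline measurement.
- State whether 30 g/day is the SD of TAC or of its change, so that the expected gain can be given as one set of figures.

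The cost is one model term and one or a few degrees of freedom. The data are already collected, and no visit, procedure or sample size has to change.

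### TAC and HDD are named as a co-primary pair, but the halved alpha and the alternative effect sizes fit an either-endpoint rule, so a split result has no defined verdict

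*Protocol article*

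**What the plan says.** **Outcomes.** Citing European regulatory guidance, the section announces a co-primary efficacy outcome: "Thus, our principal effective criteria on alcohol reduction will be both the change in TAC from baseline to week 4", together with the number of HDD.

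**Sample size calculation.** It repeats that "the EMA recommend using both TAC and the number of HDD". The calculation then rests on "an expected difference between the treatment groups of 15 g/day in total alcohol consumption or 3 days per month", a TAC standard deviation of 30 g/day and an autocorrelation of 0.3 to 0.7. It gives 82 to 122 patients, and 144 after a 20% allowance for withdrawal or non-initiation. The level is 1.25% and the power 80%. HDD has no standard deviation.

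**Statistical analysis.** "All tests will be one-sided". "The primary results will be examined at a significance level of 0.0125 (co-primary outcome"; by contrast, "For secondary outcomes, the threshold for significance will be fixed at 0.025". A mixed model is used "to estimate the effect of treatment on TAC first, and HDD second".

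TAC and HDD also appear among the secondary outcomes in Outcomes, at the end of the rTMS sessions and for every 4-week period up to week 24. Read literally, that includes weeks 1 to 4.

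**The concern.** Two success rules are possible, and each has its own alpha.

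- **Both endpoints must succeed.** Each can be tested at the full one-sided 0.025 without inflating the error rate. Halving buys nothing and costs power.
- **Either endpoint may succeed.** The level must be split, and 0.0125 each is the Bonferroni split of 0.025.

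The endpoint definition points to the first rule. The alpha and the *or* in the sample size point to the second. Suppose TAC gives p = 0.005 and HDD gives p = 0.10. Under the first rule the trial is negative; under the second it is positive. If both give p = 0.02, a both-required rule at 0.025 would succeed, while the printed threshold fails. A rule left open can be chosen after the data are seen. The meaning of the 80% power also depends on it.

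**Working it through.** **1. Reproduce 82 to 122.** Inputs from Sample size calculation: difference 15, SD 30, one-sided 0.0125, power 80%, ρ = 0.3 to 0.7. The number of repeated measurements m is not given, so it is an assumption here.

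n per group = 2(z₀.₉₈₇₅ + z₀.₈₀)² · 30² · V / 15², with V = (1 + (m − 1)ρ)/m and z-values 2.2414 and 0.8416.

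- m = 3, ρ = 0.3: V = 0.533, n = 40.6 → 41, total **82**.
- m = 3, ρ = 0.7: V = 0.800, n = 60.8 → 61, total **122**.

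Of m = 1 to 7, only m = 3 fits. One-sided 0.025 gives 68 to 102 and two-sided 0.0125 gives 96 to 144, so neither fits. (Two-sided 0.025 is numerically the same as one-sided 0.0125.) The 80% is therefore single-endpoint power for TAC at the split level.

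**2. Error rate.** Either-or at 0.0125 each gives at most 0.0125 + 0.0125 = 0.025 (0.0248 if the tests are independent). Requiring both at 0.0125 is conservative, and requiring both at 0.025 keeps the error at or below 0.025.

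**3. Power under each rule.** Assume that HDD has the same standardised effect as TAC, 15/30 = 0.5. For a 3-day difference this means an HDD SD of 3/0.5 = 6 days. Each test statistic has mean λ = 0.5 / √(V · 4/N). For N = 122 and ρ = 0.7, λ = 3.087. P(both) is the bivariate normal probability that both statistics exceed the critical value. P(at least one) = 2 × single power − P(both). Evaluable N is 122 (the plan's figure) or 115 (144 × 0.8 = 115.2). Ranges run over correlations of 0 to 0.9 between the two test statistics, which the document does not give.

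| Evaluable N | ρ | One endpoint, 0.0125 | Both, 0.0125 each | Both, 0.025 each | At least one, 0.0125 each |
|---|---|---|---|---|---|
| 122 | 0.7 | 80% | 64–75% | 76–83% | 96–85% |
| 115 | 0.7 | 77.5% | 60–72% | 72–81% | 95–83% |
| 115 | 0.5 | 85% | 73–81% | 82–88% | 98–89% |
| 115 | 0.3 | 92% | 85–90% | 92–94% | 99–95% |

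**4. HDD alone.** The SD is not in the document, so a range is shown for N = 115, ρ = 0.5 and one-sided 0.0125: Φ(3/(SD · √(2/3) · √(4/115)) − 2.2414).

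| Assumed HDD SD (days) | 5 | 6 | 7 | 8 | 9 | 10 |
|---|---|---|---|---|---|---|
| Power | 96% | 85% | 72% | 59% | 48% | 39% |

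**The case against.** The strongest reply is that the statistical parts agree with one another. A 0.0125 test level, 1.25% in the sample size, alternative effect sizes and single-endpoint power all fit an either-endpoint rule. On that reading *both* means only that two outcomes are designated primary. This is a fair reading. It removes the power shortfall, but not the defect: the rule is still unstated, and the co-primary wording with its regulatory reference points the other way.

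Four stronger readings may tempt a reader. The document does not support them.

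- **A third, sequential scheme.** The phrase about TAC first and HDD second gives the order in which effects are estimated. No gatekeeping, conditional test or passing-on of alpha is stated.
- **Inflated type I error for the primary pair.** It is controlled under either rule.
- **The 80% is simply wrong.** It is right for TAC on the plan's inputs. It falls short as a joint figure only if both endpoints are required, and mainly towards the upper autocorrelation. At ρ = 0.3, joint power exceeds 80% even at 0.0125 each.
- **HDD is underpowered.** Without an SD this cannot be shown. The range above runs from comfortable to poor.

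The week-4 overlap with the secondary outcomes is best read as a drafting slip. The stated primary threshold governs week 4, but the wording should be tidied.

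**Conclusion.** The contradiction stands on the text. The endpoint definition and the alpha imply different success rules, some current wording is wrong under either, and a trial with one positive and one null endpoint has no defined result. The harm is an undecided verdict and possibly lost power, not a false-positive risk.

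In size, at 122 evaluable and ρ = 0.7, the unstated rule moves power from 64–75% (both at 0.0125) to 85–96% (at least one). If both are required, the split alone costs about 8 to 12 percentage points. These figures assume three measurements, equal standardised effects for TAC and HDD, and test correlations of 0 to 0.9. Under an either-endpoint rule, 80% is a floor at 122 evaluable whatever the HDD effect; at 115 evaluable and ρ = 0.7 that floor is 77.5%.

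**What to change.** Before unblinding, state one rule and align the Outcomes, Sample size calculation and Statistical analysis sections with it.

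- **(a) Both required.** The trial is positive only if TAC and HDD at week 4 both favour active rTMS, each tested at one-sided 0.025. Delete 0.0125 (1.25%) and the *or*. Restate power as joint power, with an explicit HDD SD and TAC–HDD correlation.
- **(b) Either suffices.** Keep 0.0125 for each. Drop *co-primary*, and drop *both* as a condition for success. State that the 80% refers to TAC.

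Under either option, limit the secondary TAC and HDD outcomes to the end of rTMS and the periods after week 4, so that the week-4 result falls under one threshold.

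The cost is an amendment to wording and a restated power figure. Option (b) needs no more patients. Option (a) needs none if the sponsor accepts that joint power with 144 randomised may be below 80%. To secure 80% jointly at ρ = 0.7, with equal effects and 0.025 each, needs 118 to 132 evaluable for correlations of 0.8 down to 0. Dividing by 0.8 gives 148 to 165 randomised. The choice of rule is the sponsor's.
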